## Abstract

**Introduction:**

Posterior circulation ischemic stroke (PCIS) with vertigo is a common central vertigo disease that significantly hinders patients’ motivation for rehabilitation and increases the recurrence rate and mortality among stroke patients due to recurrent episodes of vertigo. Acupuncture has shown promising therapeutic effects in the treatment of PCIS with vertigo, but its underlying mechanisms remain unclear. This study is designed to investigate the impact of acupuncture on cerebral hemodynamics and brain structure in PCIS patients vertigo, and to evaluate its clinical effectiveness in managing this condition.

**Methods and design:**

This is a multicenter, randomized, controlled trial that will randomly allocate 234 participants in a 1:1:1 ratio to manual acupuncture group, sham acupuncture group, or western medication group. This trial is primarily designed as an explanatory trial, with the primary comparison being manual acupuncture vs. sham acupuncture to evaluate the specific efficacy of acupuncture; comparisons between acupuncture and western medication are regarded as secondary comparative effectiveness analyses. All groups will receive standard secondary stroke prevention. Manual and sham acupuncture will be administered five times weekly for 3 weeks (30 min/session), while the western medication group will receive oral betahistine mesilate tablets three times daily, 5 days per week, for 3 weeks. Assessments will be conducted at baseline (Week 0), post-treatment (Week 3), and at Week 11. The primary outcome is the Dizziness Handicap Inventory (DHI); secondary outcomes include the Dizziness and Anxiety Rating Scale (DARS), dizziness diaries and adverse event rate during the follow-up period. To test the *a priori* hypothesis that acupuncture improves dizziness by modulating posterior circulation hemodynamics and regional cerebral perfusion in vestibular-related brain regions, cerebral hemodynamics and brain imaging changes will be assessed using transcranial Doppler (TCD), structural magnetic resonance imaging (sMRI), and arterial spin labeling MRI (ASL-MRI) at baseline (Week 0) and post-treatment (Week 3). We specifically hypothesize that acupuncture will increase mean flow velocity (MFV) and reduce resistance index (RI) in the vertebral arteries, basilar artery, and posterior cerebral arteries, enhance regional cerebral perfusion in vestibular-related brain areas, and induce structural changes associated with vestibular compensation.

**Discussion:**

This study will provide robust evidence on the safety and efficacy of acupuncture for vertigo with PCIS. In addition, it will test a prespecified biological hypothesis that acupuncture may relieve dizziness by improving vertebrobasilar hemodynamics and regional perfusion within vestibular-related brain networks, with corresponding imaging changes associated with clinical improvement. This research aims to offer novel insights into acupuncture as a potential therapeutic approach for vertigo following PCIS.

**Clinical trial registration:**

[chictr.org.cn], identifier [ChiCTR2400087030].

## Introduction

Posterior circulation ischemic stroke (PCIS) with vertigo is one of the common types of central vertigo, accounting for approximately 20–30% of all ischemic strokes, and is frequently associated with severe dizziness and unfavorable functional recovery (1). While motor, speech, and cognitive recovery in stroke patients has received substantial therapeutic attention, chronic vertigo symptoms are frequently overlooked (2, 3). As an independent risk factor for stroke patients (4), vertigo reduces rehabilitation participation, disrupts rehabilitation progress, and even increases stroke recurrence and mortality rates, forming a vicious cycle that impairs overall post-stroke recovery (5).

Currently, for patients with PCIS accompanied by vertigo, clinicians typically use medications such as betahistine. Given the absence of disease-specific, evidence-based pharmacotherapy for vertigo associated with PCIS, we selected betahistine as the comparator in this trial. Although betahistine is most widely studied in peripheral vestibular disorders such as Ménière’s disease, it remains the most commonly prescribed agent for central vascular vertigo in clinical practice, particularly for patients with vertebrobasilar insufficiency. Betahistine acts as a partial agonist at H2 receptors and an agonist at H1 receptors, exerting significant vasodilatory effects on cerebral, coronary, and peripheral vessels, particularly the vertebrobasilar system, thereby increasing blood flow to the brain, heart, and peripheral tissues (6). Meanwhile, it acts as an H3 receptor antagonist to improve central vestibular compensation (7, 8). These dual mechanisms provide a biologically plausible rationale for its use in PCIS with vertigo. As no definitive first-line medication exists for this indication, betahistine represents the most pragmatic and clinically relevant choice to enable a direct comparison with acupuncture. However, achieving long-term control and improvement of vertigo symptoms with betahistine typically requires both high doses and prolonged administration (9). Clinical studies indicate that existing pharmacological treatments provide limited efficacy evidence for managing vertigo associated with PCIS, and symptoms frequently recur upon discontinuation of the medication (10). Additionally, polypharmacy in stroke patients may reduce adherence, increase drug resistance, and impose extra physical and psychological burdens, highlighting the critical need for safe, effective, and well-tolerated non-pharmacological interventions.

Acupuncture, recommended by the World Health Organization (WHO) as an alternative and complementary strategy for stroke management and rehabilitation (11), has shown promising efficacy and safety for post-stroke vertigo (12). However, most studies have primarily utilized acupuncture as an adjunct to western medical treatments (e.g., betahistine, flunarizine), which makes it difficult to clearly delineate the specific therapeutic effects of acupuncture itself. The clinical effectiveness of acupuncture has been questioned due to potential psychological or placebo effects, leading to concerns about the rigor of control designs in many studies. Overall, the clinical evidence supporting acupuncture for PCIS with vertigo remains limited and generally of low quality (13). Therefore, the present study is designed to provide novel insights in two key aspects. First, by independently establishing a sham acupuncture control group and a western medication control group, this trial aims to isolate the specific therapeutic effects of acupuncture as a standalone intervention, disentangling its intrinsic efficacy from non-specific factors such as concomitant drug effects or placebo responses. Second, a treatment expectation assessment will be incorporated to quantitatively evaluate the potential influence of psychological factors on treatment outcomes, an aspect seldom addressed in previous studies.

Pathophysiologically, normal brain function relies on stable metabolic processes, and stroke-induced cerebral metabolic imbalances and secondary structural changes (14). In clinical practice, post-stroke vertigo patients often experience dizziness that is not related to positional changes but rather to prolonged physical activity or sustained attention, associated with cerebral blood flow dysregulation and subsequent oxygen and glucose imbalance (15). Moreover, following ischemic strokes, structural changes in the brain, such as alterations in white matter integrity and gray matter volume, have been well-documented. Studies indicate that structural abnormalities, including infarct location and total lesion volume, may be closely linked to the occurrence of vertigo after stroke (16). In particular, lesions involving the vestibular nuclei, brainstem, cerebellum, or vestibulo-cerebellar structures may be especially relevant to dizziness symptoms (17). Nevertheless, in patients with PCIS, the severity and persistence of dizziness may not be fully explained by lesion topography alone. Residual vertebrobasilar hypoperfusion, altered neurovascular regulation, and secondary reorganization of vestibular-related brain regions may also contribute to symptom burden during recovery (18). Therefore, in the present trial, lesion location will be documented at baseline, while TCD, sMRI, and ASL-MRI will be used as complementary tools to characterize dynamic cerebral hemodynamics, regional perfusion, and structural changes associated with symptom persistence and recovery.

Hence, this study designed as a multicenter, large-sample randomized controlled trial aimed at: (1) Primary objective: To evaluate the specific efficacy and safety of manual acupuncture for PCIS with vertigo or dizziness by comparison with sham acupuncture. (2) Secondary objective: To compare the effectiveness and safety of manual acupuncture with western medication (betahistine) for PCIS with vertigo or dizziness. (3) Mechanistic objective: To test the *a priori* hypothesis that acupuncture alleviates vertigo by improving posterior circulation hemodynamics and regional cerebral perfusion in vestibular-related brain regions. Changes in TCD parameters, ASL-MRI perfusion, and sMRI structural markers will be evaluated and correlated with improvements in DHI scores.

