### TCD, sMRI and ASL-MRI outcome measures

This trial will concentrate on the following TCD, sMRI and ASL-MRI indicators (week 0, and week 3). For TCD, assessment includes measuring the mean flow velocity (MFV) and resistance index (RI) in the bilateral middle cerebral arteries (MCA), anterior cerebral arteries (ACA), posterior cerebral arteries (PCA), vertebral arteries (VA), and basilar artery (BA) for TCD. For sMRI, evaluations will encompass voxel-based whole-brain voxel-mirrored homotopic connectivity (VMHC), cortical thickness, gray matter volume (GMV), white matter volume (WMV), and total brain volume (TBV). These comprehensive assessments aim to provide detailed insights into cerebrovascular function and brain structural changes over the study period. For ASL-MRI, the following image data will be acquired: high-resolution 3D T1-weighted images for delineation of gray and white matter regions of interest (including deep gray matter structures), to support ASL data analysis and spatial normalization to a standard brain atlas. The total scanning time per MRI session will be within 15 min.

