### Sample size calculation

As reported in previous studies (8), the mean DHI score for patients treated with betahistine mesilate was 30. For the purpose of sample size estimation, we adopted the clinically meaningful difference derived from our primary comparison: manual acupuncture versus sham acupuncture, assuming a mean DHI score of 21 in the manual acupuncture group, 33 in the sham acupuncture group, with a standard deviation of 20. A 12-point difference in DHI total score between manual acupuncture and sham acupuncture was regarded as clinically meaningful, since the minimal clinically important difference (MCID) for DHI total score has been established as 11 points (26). The trial will include three groups in a 1:1:1 ratio. Using a twotailed test with a category 1 error of 0.05 and a statistical efficacy of 90%, One-Way Analysis of Variance (ANOVA) F-Tests was employed by PASS software (Power Analysis and Sample Size, version 15). The calculations indicate that a minimum of 66 participants per group is required, totaling 198 participants across all groups. Accounting for an estimated drop out rate of 15%, the total sample size should be increased to 234 participants, with at least 78 participants per group.

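### The mechanistic objective claims to test that acupuncture works by improving haemodynamics, but the only stated marker-to-symptom analysis is a correlation, which cannot test that

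*Protocol article*

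**What the plan says.** The Introduction gives the mechanistic objective as "To test the *a priori* hypothesis that acupuncture alleviates vertigo by improving posterior circulation hemodynamics and regional cerebral perfusion in vestibular-related brain regions". The next sentence gives the method: "Changes in TCD parameters, ASL-MRI perfusion, and sMRI structural markers will be evaluated and correlated with improvements in DHI scores".

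The Abstract repeats the claim twice. Under Methods and design the hypothesis to be tested is that "acupuncture improves dizziness by modulating posterior circulation hemodynamics and regional cerebral perfusion in vestibular-related brain regions". Under Discussion the trial is said to go further than efficacy: "it will test a prespecified biological hypothesis that acupuncture may relieve dizziness by improving vertebrobasilar hemodynamics and regional perfusion within vestibular-related brain networks". The Abstract also states directional predictions for the markers: "We specifically hypothesize that acupuncture will increase mean flow velocity (MFV) and reduce resistance index (RI) in the vertebral arteries, basilar artery, and posterior cerebral" vessels, together with higher regional perfusion and structural change.

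The markers are measured at Weeks 0 and 3 only, and DHI at Weeks 0, 3 and 11 (Table 1). The Statistical analysis section plans group comparisons of imaging measures and an exploratory whole-brain search for regions whose perfusion relates to vertigo improvement. Its generalized linear model carries centre and baseline values as covariates, but nothing applies that model to the marker–DHI link. No mediation analysis is described, and nothing says whether the correlation is pooled, within arm or adjusted for arm.

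**The concern.** A claim that treatment works by changing a marker has two links: treatment changes the marker, and that change produces the symptom benefit. Randomisation supports the first link. The second rests wholly on the marker–DHI analysis, and a plain correlation of two changes does not establish it under either available reading.

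- **Pooled over arms, unadjusted.** The plan predicts that acupuncture shifts both the markers and DHI. Two arm effects are enough to produce a correlation even if, within each arm, patients whose marker moved more improved no more than the others. The correlation then only restates the two group differences.
- **Within one arm.** That artefact disappears, but so does the randomised contrast. Natural recovery after stroke can improve flow and symptoms together.

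The risk is that the report presents a confirmed mechanism when the data show, at most, that acupuncture affected two things.

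**Working it through.** **1. The plan's own figure.** Sample size calculation gives the DHI assumptions: "assuming a mean DHI score of 21 in the manual acupuncture group, 33 in the sham acupuncture group, with a standard deviation of 20", and for betahistine "the mean DHI score for patients treated with betahistine mesilate was 30". The grand mean is (21 + 33 + 30)/3 = 28, and the squared deviations sum to 49 + 25 + 4 = 78. With 66 per group the noncentrality is 66 × 78/20² = 12.87. The one-way ANOVA F-test at 0.05 then has power 90.05%, so the stated 66 per group reproduces. Dropout: 66/0.85 = 77.6, rounded up to 78 per group, or 234 in all. There is no fault here.

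**2. Inputs for the pooled reading.**
- DHI effect, manual versus sham acupuncture: (33 − 21)/20 = 0.60 SD (from the plan). The plan gives this SD alongside mean scores; applying it to improvement is an assumption.
- Evaluable patients: 66 per arm, so n = 132 (from the plan).
- Marker effect d_M: not in the document; assumed at 0.5, 0.6 and 1.0 SD.
- Marker change and DHI improvement unrelated within each arm, that is, no mediation.

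**3. Correlation produced by the arm effects alone.** For two equal arms:

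ρ = 0.25·d_M·d_Y / √[(1 + 0.25·d_M²)(1 + 0.25·d_Y²)]

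- d_M = 0.5: 0.075/√(1.0625 × 1.09) = 0.070
- d_M = 0.6: 0.09/1.09 = 0.083
- d_M = 1.0: 0.15/√(1.25 × 1.09) = 0.129

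**4. How often p < 0.05.** By Fisher's z, the expected test statistic is atanh(ρ) × √(132 − 3), with √129 = 11.36. The rejection rate is the two-tail probability beyond ±1.96.

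| d_M | expected z | rejection rate (Fisher z) | simulation, pooled | simulation, arm-adjusted |
|---|---|---|---|---|
| 0.5 | 0.79 | 12.5% | 12.3% | 4.9% |
| 0.6 | 0.94 | 15.6% | 15.1% | 4.8% |
| 1.0 | 1.47 | 31.2% | 31.8% | 4.8% |

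The simulations used 10,000 trials per setting. Separate runs at 0.6 SD gave 15–17%. With no marker effect the pooled rate is 4.8%, so the inflation comes from the two arm effects.

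**5. All three arms pooled (n = 198).** The betahistine DHI mean of 30 implies an effect of (33 − 30)/20 = 0.15 SD against sham. The pooled rates are about 11–13%, 13–15% and 28–30% at the same three marker effects, depending on whether betahistine also shifts the marker.

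**6. Within the acupuncture arm only.** The rate is about 5% in every setting. This simulation contains no common cause such as recovery, so it shows only that the arm artefact is gone. The same limit applies to the arm-adjusted column.

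**The case against.** The strongest reply is that the article fixes very little. It says the changes will be correlated; it does not say they will be pooled. Pooling, adjustment and time point are details an article may leave to the analysis plan. This stands in part: a reader might infer that a pooled, unadjusted correlation is planned, and the document does not say so. The rates above are therefore conditional. What remains does not depend on that choice, because a plain correlation fails to test the stated claim whether pooled or within arm. That is a mismatch between two things the article does state.

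A second reply is that the correlation is not the whole mechanistic analysis. Correct: randomised comparisons of imaging markers are planned, and the directional predictions in the Abstract concern effects on the markers. A reader might infer that the mechanism rests on correlation alone, which would be unfair. But those comparisons address the first link only.

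Third, some wording is softer. The Abstract's Discussion speaks of imaging changes associated with improvement, and the main Discussion of exploring mechanisms. This tempers the claim, but the Introduction and both Abstract passages still say the hypothesis will be tested.

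Fourth, larger inflation can be produced. With both effects at 1.0 SD the pooled rate is about 64%. The plan assumes 0.6 SD on DHI, so the document does not support that figure.

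Finally, a reader might infer that the correlation uses Week 3 DHI, measured at the same visit as the marker. The article does not limit it to Week 3. Nor would switching to Week 11 DHI alone settle the order in time: Week 3 symptoms can persist to Week 11, and under the planned LOCF a missing Week 11 value is filled by an earlier one, often that from Week 3.

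**Conclusion.** The concern holds as a mismatch between a causal objective and an associational method. The stated analyses can show that acupuncture changes a marker and that marker and DHI move together; they cannot show that the one produces the other.

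If the correlation is pooled without adjustment, false support per marker rises from 5% to about 12% (0.5 SD marker effect), 15–17% (0.6 SD) or 31% (1.0 SD). These figures rest on the plan's DHI effect of 0.6 SD, 66 evaluable patients in each of two arms, assumed marker effects and no within-arm link. In each of these settings acupuncture does move the marker, so the false part of the conclusion is the link to symptoms. At 0.5–0.6 SD the inflation is moderate.

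The objective is not the primary one, and the primary comparison and sample size are untouched. The change is still worth making, because it is cheap and limits what the trial could wrongly conclude.

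**What to change.** 1. State that the marker–DHI association will be estimated in the manual and sham acupuncture arms, adjusted for arm, baseline DHI, baseline marker and centre.
2. Reword objective 3, and the matching text in the Abstract (Methods and design; Discussion), as an exploratory association between marker change and DHI improvement, not as a test that acupuncture works through haemodynamics.
3. If a mechanism claim is kept, report the indirect effect for manual versus sham acupuncture with a bootstrap interval and an explicit assumption of no unmeasured confounding. Week 11 DHI may serve as a supporting outcome only with Week 3 DHI in the model and without LOCF-filled Week 11 values.

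The cost is wording and a little extra analysis on data already scheduled for collection. The price is a more modest mechanistic claim. Arm adjustment removes the arm artefact but not confounding by recovery, so the adjusted association should still be reported as association.

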## Patients and methods

### Study design

This randomized, three-armed, parallel-controlled, multicenter clinical trial was approved by the Medical Ethics Committee of the Affiliated Hospital of Chengdu University of Traditional Chinese Medicine (approval number: 2024KL-021) and registered with the China Clinical Trial Registration Center (registration number: ChiCTR2400087030; https://www.chictr.org.cn/), prior to the enrollment of the first participant. The protocol adheres to the SPIRIT statement. The future trail will carry out in accordance to the Declaration of Helsinki and follow the Consolidated Standards of Reporting Trials (CONSORT) guidelines (19), including the STRICTA extension for reporting interventions in clinical trials of acupuncture (20).

All participants are coming from 3 tertiary hospitals in Sichuan Province, China: the Affiliated Hospital of Chengdu University of Traditional Chinese Medicine, Chengdu Shuangliu District Hospital of Traditional Chinese Medicine and Chengdu Longquanyi District Hospital of Traditional Chinese Medicine. The study period comprised a 1-week baseline phase, a 3-weeks treatment phase, and an 8-weeks follow-up phase. A flow chart outlining the trial design is presented in Figure 1, while details on patient enrollment, intervention, and assessment times are shown in Table 1.

**Figure 1 fig1:**
[figure not shown]
Research flow chart.

**Table 1 tab1:** Study schedule for data measurements.

Study period	Baseline	Allocation	Intervention period	Follow-up period
Time point (week)	−1	0	3	11
Enrolment and Baseline data:	Eligibility screen; informed consent; demographic characteristics; disease/combination medication history	Randomization		
Primary outcome:		DHI	DHI	DHI
Secondary outcomes:		DARS; dizziness diaries	DARS; dizziness diaries; adherence assessment	DARS; dizziness diaries
Objective hemodynamic/ imaging indicators:		TCDsMRIASL-MRI	TCDsMRIASL-MRI	
Other assessments:		Treatment expectations assessment	Safety assessment	Safety assessment

DHI, Dizziness Handicap Inventory; DARS, Dizziness and Anxiety Rating Scale; TCD, transcranial Doppler; sMRI, structural magnetic resonance imaging; ASL-MRI, arterial spin labeling MRI.

### Randomization and blinding

A random number will be generated with the R software (V.4.3.3) and concealed in opaque random envelopes. The envelopes will be prepared by a third party in advance, with the sequence number labeled on the surface and the random number and group allocation information sealed in. The random envelopes will be preserved by special personnel who are not involved in treatment and evaluation. Participants are randomly assigned in a ratio of 1:1:1 to manual acupuncture (MA) group, sham acupuncture (SA) group, and western medication (WM) group.

Given the use of two distinct acupuncture techniques in this trial, the acupuncturist will be aware of the group allocation for each participant. However, identical auxiliary devices will be used in both the acupuncture and sham acupuncture groups to maintain blinding for participants. Participants in both groups will remain unaware of their specific group assignment. Furthermore, outcome assessors and statisticians will be blinded to group allocations throughout the study to minimize bias. To maintain blinding, all researchers will undergo identical training prior to the trial, and treatments will be administered in separate rooms for each participant. It should be noted that participants in the medication group will not be blinded.

